### Intervention overview

The intervention is provision of multi-faceted implementation support to PSH buildings, with the goal of helping them implement a set of evidence-based practices to reduce tenant overdose. As detailed below, the intervention will be delivered by CSH. The implementation strategies to be tested and overdose prevention practices to be implemented and are being refined in a 1-year preparation phase. In this phase, insight to and feedback on the implementation strategies and overdose prevention practices are being gathered from multiple sources including: focus groups with PSH tenants, staff, and leaders in NYC and New York’s Capital Region; additional discussions with PSH staff and leaders from buildings participating in the study; Study Advisory Board meetings; and meetings with and review by content experts and other relevant stakeholders. In future publications we will present focus group results and the final implementation strategy and overdose prevention practice packages. In the sections that follow, we provide an overview of the anticipated implementation strategies to be tested and overdose prevention practices to be implemented.

### Implementation strategies to be tested

Each building participating in the trial will receive 6 months of support in implementing the overdose prevention practices. CSH will provide implementation support consisting of four primary strategies (see Table 1): (1) a POP (PSH Overdose Prevention) Toolkit and associated trainings, (2) tenant and staff implementation champions, (3) limited practice facilitation, and (4) learning collaboratives. These strategies—which are included in the compilation of implementation strategies from the Expert Recommendations for Implementing Change (ERIC) project [37]—were selected based on conversations between the academic study team and CSH about which implementation strategies were most likely to be accepted by and useful to PSH buildings. Together, we are calling this package of implementation support “technical assistance,” to align with language more commonly used by PSH buildings.

**Table 1 Tab1:** Implementation strategy package

Strategy	Details
PSH Overdose Prevention (POP) Toolkit	- Detailed implementation manual/blueprint for the overdose prevention practices - Will be introduced to buildings in 3 pre-recorded seminars (≈ 90 min each) - Will include planning worksheets to be used in practice facilitation sessions and educational materials related to each overdose prevention practice
Tenant and staff implementation champions	- Implementation champions “dedicate themselves to supporting, marketing, and driving through an implementation, overcoming indifference or resistance” [37] - One staff member and two tenants will be appointed as implementation champions in each building. Tenant champions will receive an honorarium - Champions will work with the practice facilitator and other building stakeholders to implement and sustain overdose prevention practices in the building
Practice facilitation	- A staff member from CSH will be trained as a practice facilitator - The practice facilitator will work with tenant and staff champions, guiding and building their capacity to implement the overdose prevention practices - Initial practice facilitation meetings: tailored support in 3 workshops (≈ 90 min each) with champions and other key building staff/leaders. Meetings will focus on key questions and setting-specific problem solving - Ongoing coaching: after initial meetings, practice facilitator will lead biweekly coaching sessions for 3 months and will remain available for technical support and less frequent check-ins for up to 3 additional months - Practice facilitation sessions will be held remotely (e.g., Zoom)
Learning collaboratives	- 5 PSH buildings in the same intervention wave will form a learning collaborative - Monthly learning collaborative meetings for 6 months, facilitated by the practice facilitator. Meetings will be attended by implementation champions and, optionally, up to 1–2 other key staff/leaders from each building - Webinar format (e.g., Zoom) with discussion of ideas, challenges, and solutions related to implementing and sustaining overdose prevention practices

*Legend*: Planned strategies for supporting PSH buildings in implementing overdose prevention practices. The full implementation strategy package will be refined and finalized during the preparation phase of the study. CSH will administer the implementation support (also being called “technical assistance,” as this term is more commonly used by supportive housing agencies) to each building during its randomly assigned 6-month intervention period

Trainings, initial practice facilitation meetings and coaching sessions, and learning collaboratives are expected to amount to approximately 20 h over the first 3 months of each 6-month technical assistance period. More limited practice facilitation will continue in the next 3 months, in addition to ongoing learning collaborative meetings. Outside of scheduled meetings, building leaders and staff and tenant implementation champions are expected to spend additional time working to implement the overdose prevention practices in their building. Overall, the amount of time for active implementation activities is moderate, and deliberately designed to maximize generalizability in PSH settings given real-world resource constraints.

#### Overdose prevention practices to be implemented

Buildings will receive support for implementing overdose prevention practices in three core categories: (1) overdose response; (2) harm reduction; and (3) support for substance use disorder (SUD) treatment. While the exact list of specific overdose prevention practices within each category is being refined in the study’s preparation phase, examples of anticipated practices are shown in Table 2.

**Table 2 Tab2:** Overdose prevention practices

Category	Overdose prevention practice examples
Overdose response	Create building-specific written overdose prevention and response plan; conduct formal debriefings after any overdose; provide support to staff and tenants related to trauma resulting from overdose; make naloxone readily available in the building; provide all tenants and staff with a naloxone kit and training on naloxone use and overdose response; systematically track information on overdoses in the building
Harm reduction	Uphold protocols that support a harm reduction model; take steps to minimize tenants using drugs alone without someone aware; train staff and tenants on harm reduction specific to the PSH environment and trends/risks related to the drug supply; have and document discussions with all tenants about safer drug use and overdose risk reduction; hold events and trainings for staff and tenants focused on reducing stigma toward people who use drugs; train staff in trauma-informed care; provide additional support for tenants during higher risk periods for overdose (e.g., transitions)
Support for SUD treatment	Educate staff and tenants about different SUD treatment types, including dispelling common myths about medication to treat opioid use disorder (MOUD); regularly assess tenant SUD treatment needs and interests; establish referral pathways to MOUD providers; provide access to peer support models; provide assistance to help tenants successfully engage in SUD treatment; provide support for tenants who are already in SUD treatment or are trying to reduce their drug use and/or who are maintaining sobriety

*Legend*: Draft planned categories and examples of specific overdose prevention practices. The complete list of overdose prevention practices will be refined and finalized during the preparation phase of the study. During the 6-month intervention period, PSH buildings will be supported in implementing these practices using the strategies described in Table 1

There has been no past research that would suggest a set of “gold standard” overdose prevention practices for PSH specifically. However, the planned overdose prevention strategies outlined above have either been studied in other settings or are generally accepted as best practices, including for structurally marginalized populations such as people experiencing homelessness [38–48]. We modeled an initial list of overdose prevention practices on an overdose prevention practice package developed by an interagency workgroup for use in isolation and quarantine hotels for people experiencing homelessness during the COVID-19 pandemic. We felt this package would be promising for adaptation to PSH settings because it was comprehensive, based on expert consensus on evidence-based practices, and developed for settings bearing similarities to PSH (e.g., serving a high-risk and stigmatized population, having private rooms where overdose is possible behind closed doors). We made initial adaptations based on results from New York PSH leader surveys in the project’s exploratory phase [20], which provided insight to inform overdose prevention in PSH. For example, the surveys revealed stigma and misunderstanding related to medication for opioid use disorder, a lack of defined referral pathways for SUD treatment, and gaps in PSH staff training on naloxone use.

We are further adapting the package of overdose prevention practices for PSH settings in a 1-year preparation phase, including gathering feedback from focus groups with PSH tenants, staff, and leaders in NYC and New York’s Capital Region, as well as from the Study Advisory Board, content experts, and other relevant stakeholders. We will adapt, refine, and finalize the list of overdose prevention practices based on this feedback. We hypothesize that adapting the overdose prevention practices for the specific PSH setting will increase the likelihood that they are viewed as acceptable and appropriate by PSH staff and tenants, and that they are implemented with fidelity and sustained.

Buildings participating in the study will receive education, training, and support for implementing the overdose prevention practices during their randomly assigned 6-month intervention (technical assistance) period. While buildings will be trained on and receive support in implementing each of the overdose prevention practices, we will not require and do not anticipate that all buildings will implement every practice. The primary goal of the study is to examine how successful buildings are in implementing the practices and we expect there to be heterogeneity across buildings.

### Randomization

Buildings will be randomly assigned to one of four sequential 6-month intervention waves (five buildings per wave). With the stepped-wedge design, all study buildings will begin in the control condition. Buildings are randomly assigned to cross over at different times, with all eventually receiving the intervention. See Fig. 1 for a schematic of the stepped-wedge cluster RCT design.

Randomization will be conducted by the study statistician, who will not have contact with the PSH buildings. There is no stratification of randomization. Buildings will be notified of their assigned intervention wave before the first wave starts.

**Fig. 1 Fig1:**
[figure not shown]
POP study stepped-wedge RCT design Legend: Schematic of the stepped-wedge RCT design. Each building will be randomized to one of 4 waves during which they will receive the 6-month technical assistance intervention. There is a 1-month break/buffer period between each wave to facilitate measurement (e.g., staff surveys and fidelity checklist completion) and preparation for the subsequent wave. Not shown in the figure is that formal measurement of sustainment will occur for each building in the 8th month following wave completion

### Outcomes

As a hybrid type 3 effectiveness-implementation trial, this study aims primarily to examine implementation outcomes and secondarily to explore clinical effectiveness.

#### Primary outcome

The primary outcome is building-level fidelity to the overdose prevention practices. This outcome will be measured with a scored building-level fidelity checklist completed by two raters blinded to building wave assignment. Checklists will be completed for each participating building at five time points: once before the first intervention wave begins, and once as each of the four waves ends. Raters will complete the fidelity checklists using a combination of program material review (e.g., lease language, building overdose prevention plan, training calendar and attendance logs), self-assessment surveys completed by building leaders and key staff, and environmental observation when possible/applicable (e.g., presence of naloxone in the building). For each overdose prevention practice, buildings will receive a fidelity checklist score of 0 (not implemented), 1 (partial implementation), or 2 (full implementation). Scores will be benchmarked to defined, objective, measurable criteria. The two raters will independently complete checklists, and their scores averaged. The primary outcome is the average sum score on the fidelity checklist, treated as a continuous variable. The range of possible scores will depend on the final number of overdose prevention practices (for example, if there are 15 final overdose prevention practices, fidelity checklist scores would range from 0 to 30). Secondary analyses will examine fidelity checklist sub-scores (e.g., for specific overdose prevention practice categories).

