#### Secondary and exploratory outcomes

Secondary implementation and effectiveness outcomes, and exploratory effectiveness outcomes, are summarized in Tables 3 and 4. Secondary and exploratory outcomes will be examined using (1) PSH staff surveys, (2) Medicaid data analysis, and (3) PSH tenant surveys.

**Table 3 Tab3:** Secondary outcomes

Outcome	Measure	Data source	Timepoint(s)
*Secondary implementation outcomes*			
Adoption	Self-reported adoption of overdose prevention practices	Building self-assessment surveys^a^	Before first intervention wave, then as each of the 4 waves ends (5 timepoints)
Acceptability	Acceptability of intervention measure [49]	Staff surveys	5 timepoints as above
Appropriateness	Intervention appropriateness measure [49]	Staff surveys	5 timepoints as above
Feasibility	Feasibility of intervention measure [49]	Staff surveys	5 timepoints as above
Organizational priority	Adapted from Klein, et al. [50]	Staff surveys	5 timepoints as above
Sustainment	Fidelity checklist (see “Primary outcome” section)	Two blinded raters	8th month after end of each intervention wave^b^
*Secondary effectiveness outcomes*			
Staff knowledge about OD risk	Brief Opioid Overdose Knowledge (BOOK) Survey [51]	Staff surveys	5 timepoints as above
Staff stigma	Perceived Stigma Toward Substance Users Scale [52]	Staff surveys	5 timepoints as above
Tenant substance use emergency department (ED) visits	Visit diagnosis ICD-10 codes including poisoning, abuse, or dependence for alcohol or any drug (AHRQ HCUP classification list) [53]. Exploratory analyses will examine visits with specific diagnosis of poisoning (OD)	Medicaid data	5 timepoints as above plus 6th timepoint 6 months later
Tenant medication for opioid use disorder (MOUD) receipt	Tenant receipt of MOUD, MOUD initiation (new pharmacy claims) and adherence [54, 55]	Medicaid data	6 timepoints as above
Tenant specialty SUD treatment	Outpatient, inpatient, detoxification	Medicaid data	6 timepoints as above

*Legend*: Table shows secondary implementation and effectiveness outcomes for the stepped-wedge cluster RCT. Secondary implementation outcomes are measured via PSH staff surveys, except as otherwise noted. Secondary effectiveness outcomes are measured via PSH staff surveys and analysis of Medicaid claims data for PSH tenants

^a^Selected building leaders and key staff (e.g., staff champions) will complete self-assessment surveys as described in the “Primary outcome” section

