### Statistical analysis

To estimate effects of the intervention on the primary outcome, we will use a linear mixed model that incorporates both within- and between-cluster information and accounts for secular temporal trends. In particular, to assess the intervention effect, we will use a model with random site effects of the form: *Y*_it_ = μ + β_1_t + β_2_I_*it*_ + β_3_I_*it*_(*t* – s_*i*_) + b_*i*_ where *Y*_*it*_ is the fidelity checklist score in building *i* during period t, for t ∈ (0, 1, …, 4). Each period is 6 months; *t* = 0 is the first 6-month period. *I*_it_ is an indicator variable; I_*it*_ = 1 if building *i* has been assigned to implementation at period t and *I*_it_ = 0 otherwise. s is the period when implementation begins for building *i*. b_*i*_ is a random effect associated with each building *i* (the deviation of the intercept for the building from the overall intercept μ). Models will take into account a general time trend and allow for the intervention effects to grow over time following implementation. Models will be fit using the lme4 package using R software. Each hypothesis will be tested using a two-sided level of significance α = 0.05. Similar models will be used for analysis of the secondary implementation outcomes.

Implementation sustainment will be measured in the 8th month after the conclusion of each 6-month intervention wave. Paired-samples *t* tests will be used to compare each building’s fidelity scores at the end of its control period with scores during the sustainment period. For buildings assigned to early waves, there is also an opportunity to measure longer term (> 12 months) sustainment within the study measurement period.

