### Power and sample size

With 20 buildings participating in the study and 4 “steps” or waves in the stepped-wedge RCT (i.e., *n* = 100 observations over time across all buildings given 5 total time points per building), we will have at least 80% power to detect an increase of approximately two-thirds of a standard deviation (*d* = 0.69) or larger in the primary implementation outcome, a meaningful and feasible difference. This assumes a moderate correlation between scores for the same building at different time points (ICC = 0.5), reflecting stable differences among buildings. Even in the unlikely event that we do not retain 20 buildings in the study, with 16 buildings we would still have at least 80% power to detect an increase of about three-quarters of a standard deviation (*d* = 0.77) in the primary implementation outcome. To make these effect sizes more concrete, if the checklist score had a standard deviation of 8 and an average score of 15 under the control condition, the stepped-wedge design has 80% power to detect an increase of about 5 to 6 points on the checklist score (e.g., an increase from 15 to 20).

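### Blinding the raters to wave cannot by itself protect the primary fidelity score from differential reporting by building staff who know their wave

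*Protocol article*

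**What the plan says.** Under Primary outcome, each building is scored at five time points on a "scored building-level fidelity checklist completed by two raters blinded to building wave assignment". The raters draw on three kinds of evidence: program materials, among them the "training calendar and attendance logs"; self-assessment surveys from building leaders and key staff; and observation of the environment where possible. Each practice is scored 0, 1 or 2 against objective criteria, and the two raters' independent scores are averaged.

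Footnote a to Table 3 says who fills in the surveys: "Selected building leaders and key staff (e.g., staff champions) will complete self-assessment surveys". Table 1 lists champions as one of the four implementation strategies under test, and its legend says the package is delivered during the building's own assigned period. Under Randomization, "Buildings will be notified of their assigned intervention wave before the first wave starts".

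The limitations part of the Discussion admits that the checklist has not been validated and cites the two blinded raters among the steps that give it rigour. It mentions social desirability bias for tenant surveys only.

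**The concern.** Masking the rater protects against bias that arises in the act of scoring. It does nothing about bias in the evidence that the rater is given. Here part of that evidence is written by people who know whether their building has had technical assistance, and one of them may hold a role whose purpose is to promote the practices. Both raters read the same surveys, so averaging their scores leaves a shared error untouched.

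In a stepped-wedge trial this matters because a change in reporting that starts with the intervention has the same time pattern as the intervention effect. The time trend in the model does not absorb it. A positive primary result could then reflect better practice, more generous reporting, or both, and the primary analysis could not tell them apart. Self-reported adoption, a secondary outcome, comes from the same surveys and so offers no independent check.

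**Working it through.** **Inputs.** Four waves of five buildings ("one of four sequential 6-month intervention waves (five buildings per wave"), five time points, 100 scores. "Each hypothesis will be tested using a two-sided level of significance" of 0.05. ICC: "This assumes a moderate correlation between scores for the same building at different time points (ICC = 0.5". Target: "we will have at least 80% power to detect an increase of approximately two-thirds of a standard deviation", d = 0.69, or d = 0.77 with 16 buildings. The illustrative SD is 8 points (Power and sample size). I assume that crossover is first visible at the assessment closing the building's own wave.

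**Step 1: reproduce the plan's figure.** Set the total variance to 1, so the between-building variance τ² = 0.5 and the residual variance σ² = 0.5. The Hussey-Hughes variance of the intervention coefficient is

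Var = Nσ²(σ² + Tτ²) / [(NU − W)σ² + (U² + NTU − TW − NV)τ²]

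with N = 20 and T = 5, and
- U = 5 + 10 + 15 + 20 = 50 post-crossover scores
- W = 5² + 10² + 15² + 20² = 750
- V = 5 × (4² + 3² + 2² + 1²) = 150

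Numerator: 20 × 0.5 × 3 = 30. Denominator: (1000 − 750) × 0.5 + (2500 + 5000 − 3750 − 3000) × 0.5 = 125 + 375 = 500. Var = 0.06 and SE = 0.245 SD.

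Detectable d at 80% power = (1.960 + 0.842) × 0.245 = 0.686. Power at d = 0.69 is 80.4%. The same formula for 16 buildings gives SE 0.274 and d = 0.767. Linear time gives the same SE. Adding the protocol's growth term gives d = 0.692 to 0.694 for 20 buildings. The stated power is reproduced. At SD 8, 0.69 SD is 5.5 points and one SE is 0.245 × 8 = 1.96 points.

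**Step 2: where a reporting shift goes.** Suppose every post-crossover score is raised by b points. The data then contain an extra b × I_it. I_it is itself a column of the model, so least squares, weighted or not, returns β₂ + b and leaves the time trend and β₃ unchanged. Fitting the protocol's linear-time model to a shift of 1 gives a change in β₂ of exactly 1, with or without the growth term.

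**Step 3: consequence with no true effect.** P(significant) = Φ(−1.96 + b/(8 × 0.245)) + Φ(−1.96 − b/(8 × 0.245)).

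| Assumed shift b (points) | In SD units | Chance of a significant result |
|---|---|---|
| 0 | 0 | 5.0% |
| 0.5 | 0.062 | 5.7% |
| 1 | 0.125 | 8.0% |
| 2 | 0.250 | 17.5% |
| 3 | 0.375 | 33% |

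The growth term barely changes these figures. The values of b are assumptions.

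**Step 4: assessments where condition is obvious.** At the first assessment all 20 buildings are in control, and at the last all 20 have crossed over, so raters can know the condition for 40 of 100 scores. A 1-point shift common to all buildings at either assessment moves β₂ by 0.00 without the growth term. With it, β₂ moves by 0.04 and β₃ by 0.17. That count therefore does not measure bias in β₂. The mechanism that matters is the one in Step 2.

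**The case against.** The strongest reply is that nothing shows the blinding to be broken. A reader might infer that the logs reveal the wave, that champions exist only after crossover, and hence that the safeguard fails. The documents support none of these:

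- The article does not say that logs reach raters unmasked, and a condensed article may leave masking steps to the full protocol.
- Training calendars and attendance records are proper evidence, since staff and tenant training is among the practices in Table 2. A rater who sees them is partly seeing the outcome itself.
- No appointment date for champions is given. The Fig. 1 legend allows preparation in the buffer month before a wave. Champions are only an example of respondents, and the same person may have answered earlier as key staff.
- Scores use objective benchmarks, and surveys are combined with documents and, where possible, observation. No item is said to rest on self-report alone, so the bias may be small; at 0.5 points the error rate hardly moves.
- The baseline self-assessment may already precede wave notification, since the article does not state the order.

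All of this stands, and it limits the claim. It does not remove the core point. The choice of informant is stated in the article, so it is not a detail left to another document. Even with perfect redaction, raters would still be using reports from staff who know their wave. Benchmarks govern how evidence is scored, not whether a self-report is accurate.

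**Conclusion.** The concern holds in a limited form: rater blinding is worth having but is not enough on its own to protect the primary outcome. It leaves open differential reporting by unblinded staff, possibly including champions, and any such shift beginning at crossover enters β₂ in full. Whether it occurs, and how large it would be, cannot be learned from the documents. Under assumed shifts of 0.5 to 3 points, with no true effect, SD 8 and ICC 0.5, the chance of a significant result runs from about 6% to 33%. The power calculation is sound and is not in question. The point is worth acting on because the remedy is inexpensive and changes what a positive result can support.

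**What to change.** - In Primary outcome and Table 3 footnote a, set the self-assessment respondent roles for each building before randomisation and keep them the same at all five assessments. Respondents should not be chosen because they are champions.
- Collect the baseline self-assessment before buildings are told their wave, and state that order.
- Remove references to wave or technical assistance from the packets given to raters, except where this would remove evidence of the practice itself.
- Pre-specify a fidelity score from documents and observation only, as a sensitivity analysis of the primary outcome under the same model.
- State in the limitations that blinded raters do not remove reporting bias from staff who know their wave.

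The cost is protocol wording and light redaction work, with no new assessor. The drawback is less detailed information on items that depend on self-report.
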